### Sample size and recruitment

2.4

Based on preliminary 12-week intervention data from the previous Diactive-1 trial, the between-group difference in handgrip strength z-score was 0.24 units, corresponding to an approximate standardized effect size of Cohen’s d = 0.56 (10). Using G*Power for an independent-samples comparison with a two-sided α = 0.05, 134 evaluable participants (67 per group) would provide 89.6% power, rounded to approximately 90% (27). After allowing for an anticipated attrition rate of 15%, the recruitment target was set at 158 children and adolescents in total, with 79 participants allocated to the intervention group and 79 to the usual-care group (28). Sampling will be extended until the end of the recruitment period, incorporating as many participants as possible.

Because participants will be individually randomized within hospitals, this is not a cluster-randomized trial. Nevertheless, hospital-level effects will be accounted for in the planned mixed-effects analyses by including hospital as a random effect. As the actual hospital-level ICC is not yet known, a conservative *a priori* sensitivity analysis was conducted using the design effect DE = 1+(m−1)×ICC. Assuming a mean hospital size of approximately 14.5 participants and 15% attrition, ICC values of 0.01, 0.02, and 0.05 corresponded to effective sample sizes of approximately 120, 107, and 81 participants, with estimated powers of approximately 86%, 82%, and 70%, respectively. Thus, the planned recruitment is expected to retain more than 80% power under hospital-level ICC values of up to 0.02, whereas greater clustering would result in reduced power. Recruitment may continue beyond the target sample until the end of the prespecified recruitment period.

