### Statistical analysis

2.15

The R version and packages used will be reported. Cross-sectional analyses with baseline data will follow the STROBE statement, while the final reporting of the RCT will adhere to CONSORT 2025 (62). A two-sided α level of 0.05 will be used to determine statistical significance for the primary outcome.

Normality, descriptive statistics and group differences: Distributional properties of continuous variables will be evaluated through graphical inspection (i.e., histograms and Q–Q plots) and formally assessed using the Shapiro–Wilk test when appropriate. Homogeneity of variance will be examined using Levene’s test. Continuous variables will be summarized as mean ± standard deviation (SD) when approximately normally distributed, or as median and interquartile range (IQR) otherwise. Categorical variables will be presented as absolute and relative frequencies. Baseline characteristics will be summarized by randomized group using descriptive statistics, without formal hypothesis testing. Any baseline differences will be interpreted descriptively and clinically.

Missing data: Missing data will be examined using graphical and tabular summaries by variable, treatment group, and time point. The number and percentage of missing observations and missingness patterns will be reported separately by randomized group. Compatibility with a missing completely at random (MCAR) mechanism will be assessed using Little’s MCAR test, together with comparisons of baseline characteristics between participants with and without missing outcome data as a supplementary analysis. A missing-at-random (MAR) mechanism will be explored by modeling missingness indicators as a function of observed variables. A missing-not-at-random (MNAR) mechanism will be considered when missingness remains plausibly related to unobserved values or post-randomization events not fully explained by observed data.

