Effect of the intervention: The intervention effect will be estimated for the primary outcome using linear mixed-effects models under the ITT principle, with participants analyzed according to randomized allocation. Baseline and 12-week outcome values will be jointly modeled as repeated outcome measurements using data in long format. Models will include fixed effects for group, time, and the group × time interaction, with random intercepts for hospital and participant nested within hospital. Because baseline outcome values are included as repeated measurements, they will not be entered as separate covariates. The primary treatment effect will be estimated from the group × time interaction, representing the between-group difference in change from baseline to 12 weeks (i.e., over time). The same modeling framework will be applied to the prespecified secondary continuous outcomes, with correction for multiple testing within outcome families using the Benjamini–Hochberg false discovery rate procedure (66).

The primary model for handgrip strength will include no additional covariates. Prespecified adjusted models for glycemic outcomes will additionally include baseline daily insulin dose and baseline carbohydrate intake, whereas models for daily insulin dose will include baseline carbohydrate intake. These covariates were selected *a priori* because of their established prognostic relationships with the corresponding outcomes. No other covariates will be included in these prespecified models (67). Any additional unplanned adjusted analyses will be clearly identified as *post hoc* sensitivity analyses and will not be selected solely on the basis of observed baseline differences between groups (62).

In addition to the primary ITT analysis, per-protocol (PP) analyses will be conducted including intervention participants who complete an average of at least two resistance-training sessions per week during the 12-week intervention (68), provided that these sessions are reasonably distributed across the intervention period rather than concentrated in a limited number of weeks, and usual-care participants with available primary outcome data and no major protocol deviations.

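### The prespecified insulin and carbohydrate adjustment for the key secondary outcomes drops out of the group × time effect, and its covariates are recorded after randomisation

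*Protocol article*

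**What the plan says.** All of the model specification is in section 2.15 of the protocol article, under the effect of the intervention.

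- **Model.** Baseline and week-12 values are both outcomes. Fixed effects are group, time and their product; random intercepts are for hospital and for participant within hospital. "The primary treatment effect will be estimated from the group × time interaction". The secondary continuous outcomes use the same framework.
- **Covariates.** "Prespecified adjusted models for glycemic outcomes will additionally include baseline daily insulin dose and baseline carbohydrate intake"; daily insulin dose is adjusted for baseline carbohydrate intake. The reason given is their prognostic relation to these outcomes. The list is closed: "No other covariates will be included in these prespecified models". No covariate × time term is mentioned. The primary handgrip model has no covariates.
- **Status.** Section 2.10 makes glycemic stability and insulin requirements the key secondary outcomes.
- **Timing.** Section 2.5 randomises after the baseline clinical visit and before the 7-day diabetes record. Section 2.10.2 takes insulin and carbohydrate values from the 7 days after the visit, for AID users and for everyone else. The note to Table 2 confirms that this record falls after randomisation but before the app is activated. Section 2.5 says that participants and clinicians are not blinded.

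**The concern.** A prognostic covariate is prespecified to sharpen the effect estimate, or to protect it against chance imbalance. In a two-time-point model whose effect is a difference in change, a covariate that is constant over time can do either only if it is allowed to act on the change. As a main effect it acts on the level, which the contrast has already removed. The stated purpose is therefore not served for the outcomes that rank directly below the primary one. The paper would carry results described as adjusted for insulin and carbohydrate whose effect estimates are, in substance, unadjusted.

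The timing adds a second difficulty. If the model is changed so that the covariates do act on the effect, the effect then depends on values recorded by people who already know their allocation.

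**Working it through.** **1. The plan's own figures.** Section 2.4 states that "134 evaluable participants (67 per group) would provide 89.6% power" at d = 0.56 and two-sided α = 0.05. The noncentral t calculation gives 89.57% (normal approximation 90.0%). The target is 134 / 0.85 = 157.6, rounded up to 158, as stated. Both reproduce. They concern handgrip strength and do not depend on this point; they supply the sample size and the 15% attrition used below.

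**2. Algebra, complete data.** For participant i in hospital h with covariate x:

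- baseline: Y0 = a + b·g + c·x + u_h + u_i + e0
- week 12: Y1 = a + b·g + τ + δ·g + c·x + u_h + u_i + e1
- change: Y1 − Y0 = τ + δ·g + (e1 − e0)

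The term c·x cancels, as do both random intercepts. The estimate of δ is the difference between groups in mean change, whatever c is. Its variance is 2σ²(1/79 + 1/79), where σ is the within-participant residual SD. With an assumed σ = 5 this is 100/79 = 1.2658, so SE = 1.1251.

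**3. Numerical check.** Inputs from the article: 158 participants, 79 per group, 11 hospitals, 15% attrition. Assumed, because the article gives none: residual SD 5, participant SD 7, hospital SD 2, treatment effect 3, and two covariates with effects −5 and −3 per SD. The group × time term was estimated by GLS with known variance components and both random intercepts, 60 replicates per scenario.

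| Scenario | Mean SE, no covariates | Mean SE, main effects | Shift in estimate |
|---|---|---|---|
| Complete data | 1.1251 | 1.1251 | below 1e-12 |
| 15% missing at week 12 | 1.2112 | 1.2066 | mean 0.084, maximum 0.278 |

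At 15% attrition:

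- SE ratio: 1.2066 / 1.2112 = 0.996, a fall of 0.4%
- mean shift: 0.084 / 1.2112 = 7% of an SE
- largest shift in 60 replicates: 0.278 / 1.2112 = 23% of an SE

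Imbalance is not corrected either. With complete data, a 0.5 SD group difference in a covariate worth 2 units of change per SD, and a true effect of 3, both versions average 3.906. The expected shift of 0.5 × 2 = 1 passes through untouched.

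**4. REML fits** (participant intercept, complete data). In one data set the effect is 4.0271 (SE 1.2226) without covariates and 4.0271 (SE 1.2226) with main effects; only the baseline group term moves, from −1.70 to −0.99. With covariate × time terms it becomes 3.9934 (SE 1.2359). In another data set it goes from 1.6775, with or without main effects, to 2.0958. The covariates reach the effect only through the time interaction. Here they did not predict change, so the SE rose slightly.

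**5. What a working adjustment could gain.** If r is the correlation of a covariate with change, the variance falls by roughly r². The article gives no r, so this is a range:

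| Assumed r | Variance reduction |
|---|---|
| 0.1 | about 1% |
| 0.3 | about 9% |
| 0.58 | about 34% |

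**6. Timing, side by side.** Section 2.5: randomise, then the 7-day record. Section 2.10.2: insulin and carbohydrate come from that record for both AID and non-AID users. Section 2.11: the app is activated only after the record is verified. So both covariates, and the baseline value of the insulin outcome itself, follow randomisation but precede the app. The 14-day glucose baseline in section 2.10.1 precedes the visit, and so precedes randomisation.

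**The case against.** The strongest reply is that the article never says main effects only. The closed list covers variables, not terms, and a condensed article may leave exact terms to an analysis plan. That is fair as far as it goes. But the article lists the fixed effects, says the covariates are added to them, and names interactions where it wants them (effect modification, also in section 2.15). Main effects are the plain reading. If covariate × time terms are intended, one clause would settle the first half of this point.

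Second, the covariates are not wholly without effect. They change the adjusted means at each visit and the baseline group term. With dropouts they can support the missing-at-random assumption, and a single data set may move by up to about a quarter of an SE. This stands, but it is not the reason the article gives for including them.

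Third, the timing is openly stated and no participant has used the app by then. That also stands. What remains is knowledge of allocation while doses and carbohydrate are being recorded. While the covariates enter as main effects, their timing cannot materially distort the effect.

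Stronger readings go too far. A reader might infer that the key secondary effects are biased; cancellation causes no bias. A reader might infer that a third of the variance is being given away; that needs r near 0.58, for which the article offers no support, since prognostic value for the level of an outcome need not extend to its change. A reader might also suppose that the authors offer the adjusted models as a robustness check; the article does not say so.

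**Conclusion.** The point holds in limited form and should be corrected. On the plain reading, the prespecified adjustment leaves the glycemic and insulin effects exactly as they are with complete data and almost as they are at 15% attrition. The complete-data result is an identity and needs no assumption beyond two time points, random intercepts and main-effect covariates. The attrition figures rest on assumed SDs and covariate effects, with week-12 values missing at random across participants. The loss is an adjustment that does not do its stated job, plus whatever precision a working one would bring, which may be negligible. Validity is not at stake, and neither the primary handgrip analysis nor the sample size is touched. The post-randomisation recording applies to all participants, whatever their insulin delivery. It becomes material once the covariates are made to act on the effect, and it affects the insulin outcome's own baseline in any case.

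**What to change.** **Model.** For the glycemic and insulin outcomes, specify ANCOVA of the week-12 value on its own baseline plus the named covariates, keeping the hospital random intercept. Equivalently, add covariate × time terms in a longitudinal model with a common baseline mean. The longitudinal form fits section 2.15 better, because it keeps participants without a week-12 value; at present the common-baseline model appears there only as an optional sensitivity analysis. The cost is a sentence in the specification and one or two degrees of freedom.

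**Timing.** Choose one:

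- Run the automated randomisation after the 7-day record has been verified. The app is not activated before then anyway, so intervention start need not move. This is a procedural change to sections 2.5 and 2.11, Table 2 and the platform, not an edit to one line. It also makes the insulin outcome's baseline a true pre-randomisation value.
- Drop the two covariates, adjust glycemic outcomes only for their own 14-day pre-visit baseline, and do not describe results as adjusted for insulin and carbohydrate. This costs nothing in trial conduct, but the insulin outcome's baseline stays post-randomisation and should be reported as such. The 14-day pre-visit insulin data cannot fill the gap, because section 2.10.2 provides them for AID users only.

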#### Physical literacy

2.10.7

Perceived physical literacy will be assessed using the Spanish Perceived Physical Literacy Instrument for Adolescents (S-PPLI), a culturally adapted and validated version of the Perceived Physical Literacy Instrument for use in Spanish adolescents. The S-PPLI has shown adequate construct validity and reliability (46).

The S-PPLI comprises 9 items across three 3-item factors. Each item is scored on a 5-point Likert scale from 1 (“strongly disagree”) to 5 (“strongly agree”). Factor scores are obtained by summing their three items, ranging from 3 to 15 points. The global S-PPLI score is the sum of all nine items, or the three factor scores, ranging from 9 to 45 points, with higher scores indicating greater perceived physical literacy.

The global S-PPLI score will be analyzed as a continuous variable, with factor-specific scores used to describe the three perceived physical literacy components. When categorical interpretation is needed, previously used cut-offs will classify participants as low (9–31), moderate (32–36), or high (37–45) perceived physical literacy.

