#### Screening for eating disorders

2.10.15

The risk of having eating disorders will be assessed by the Sick, Control, One, Fat, Food (SCOFF) questionnaire, a five-question test that can be self-administered with an acceptable sensitivity and specificity (60). The Spanish SCOFF questionnaire version has been validated for its use in primary care settings (60). A score ≥2 will indicate risk of eating disorders.

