Unstandardized coefficients with 95% confidence intervals (CIs) will be used to estimate marginal means and group contrasts over time, which will be reported as mean differences (MDs). Standardized effect sizes, including Cohen’s d when appropriate, will be reported as complementary measures (69). For categorical outcomes, between-group effects will be estimated using risk differences (RDs) and relative risks (RRs), with 95% confidence intervals. When clinically interpretable, the number needed to treat, or harm, will be calculated from absolute risk differences. Effect sizes for differences in proportions will be estimated using Cohen’s *h*.

Model diagnostics will be examined to assess distributional assumptions, heteroscedasticity, and influential observations. If substantial departures are detected, robust linear mixed-effects models preserving the same fixed- and random-effects structure as the primary models will be considered. Sensitivity analyses may include restricted longitudinal data analysis under a common-baseline assumption of baseline variables showing clinically relevant imbalance between groups (70). Effect modification by sex, pubertal status, insulin delivery modality, insulin type, and CGM system will be explored by adding interaction terms to the primary model. These analyses will be considered exploratory.

Other exploratory analyses: Exploratory analyses will examine whether the magnitude of the intervention effect varies according to intervention exposure, adherence, and training-related characteristics. Dose–response analyses will use app-derived indicators of intervention exposure, including training frequency, completion of prescribed sessions, accumulated training volume, session duration, active and recovery times, training time, training type, and, when available, heart-rate metrics or perceived exertion. We will also explore whether within-participant changes in the primary and secondary outcomes are associated with changes in other clinical, behavioral, and physical-fitness variables. These change–change associations will be examined using regression models adjusted for treatment group, baseline values, hospital, and other relevant prespecified covariates. All such analyses will be considered exploratory and will not be interpreted as providing evidence of causal relationships.

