Moreover, participants will be classified as responders or non-responders according to prespecified thresholds based on clinical guidelines (38), or minimally relevant standardized effect sizes (71), with the direction of beneficial response defined separately for each outcome. Response prevalence will be calculated by treatment group and compared using the χ² test. Additional longitudinal models may include responder status interaction to explore whether intervention effects differ between responder categories. To identify baseline profiles associated with response, exploratory regression models will be fitted. These analyses will be considered hypothesis-generating.

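### Categorical outcomes are given no baseline term although baseline status is collected, so the planned risk differences and relative risks are probably less precise than they could be

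*Protocol article*

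**What the plan says.** All statements are from the protocol article.

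- **Continuous outcomes (2.15).** "Baseline and 12-week outcome values will be jointly modeled as repeated outcome measurements using data in long format", with the treatment effect taken from the group-by-time interaction. The scope is then set: "The same modeling framework will be applied to the prespecified secondary continuous outcomes".
- **Categorical outcomes (2.15).** "For categorical outcomes, between-group effects will be estimated using risk differences (RDs) and relative risks (RRs), with 95% confidence intervals". The number needed to treat or harm comes from absolute risk differences, and Cohen's h is the effect size for proportions. No estimator, time point or covariate is named.
- **Responder status (2.15).** "Response prevalence will be calculated by treatment group and compared using the χ² test". Thresholds come from clinical guidelines or from minimally relevant standardized effect sizes, and "These analyses will be considered hypothesis-generating".
- **Which outcomes could be categorical.** Section 2.10.1 lists glycemic targets. Section 2.10.15 gives SCOFF a binary reading: "A score ≥2 will indicate risk of eating disorders". KIDMED (2.10.14) has three levels. S-PPLI (2.10.7) has three levels for use when needed, but "The global S-PPLI score will be analyzed as a continuous variable". Table 2 schedules all of these measures at baseline and at 12 weeks.
- **Adjustment elsewhere (2.15).** The change–change regressions name baseline values and hospital as adjusters. Unplanned adjusted analyses are to be labelled post hoc.

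**The concern.** The plan uses baseline information for continuous outcomes and names none for categorical ones. Risk differences, relative risks, Cohen's h and a χ² test read most naturally as a comparison of two observed proportions. Where a binary status persists from baseline to week 12, part of the variance of that comparison is predictable from data the trial already holds, and leaving it in widens the interval for no benefit.

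Two further consequences follow. Allocation is not stratified (2.5), so baseline status can differ between arms by chance. Given such a difference, an unadjusted risk difference moves with it, whereas the continuous analysis models change from baseline; the two versions of one measure could then give different impressions. Also, if adjustment is not prespecified, the protocol's own rule would label it post hoc when added later.

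**Working it through.** **The plan's own figures.** No figure is given for any categorical outcome. Section 2.4 gives 67 evaluable per group with 89.6% power for the continuous primary outcome at d = 0.56 and two-sided α = 0.05. The noncentral t gives 89.57%, and 134 / 0.85 = 157.6, rounded up to 158. Both reproduce. Only n = 67 per arm is carried forward.

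**Assumptions not in the documents.** Week-12 prevalence p = 0.35 (0.20 and 0.50 as a range). Correlation phi between baseline and week-12 binary status from 0 to 0.7.

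**Unadjusted precision.** SE = √(2p(1−p)/n) = √(2 × 0.35 × 0.65 / 67) = 0.0824. The 95% half-width is 1.96 × 0.0824 = 16.2 percentage points (13.5 at p = 0.20; 16.9 at p = 0.50).

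**Adjusted precision.** In large samples, variance adjusted = (1 − phi²) × variance unadjusted. The half-width is multiplied by √(1 − phi²), and the equivalent gain in sample size is 1/(1 − phi²) − 1. The ratio does not depend on p.

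| phi | Variance ratio | Adjusted half-width (points) | Equivalent gain in n | Simulated power, true RD 0.15: unadjusted / adjusted | Shift in unadjusted RD per 10-point baseline imbalance |
|---|---|---|---|---|---|
| 0 | 1.00 | 16.2 | 0% | 42.5% / 42.4% | about 0 |
| 0.3 | 0.91 | 15.4 | 10% | 41.8% / 45.7% | about 3 points |
| 0.5 | 0.75 | 14.0 | 33% | 41.6% / 52.4% | about 5 points |
| 0.6 | 0.64 | 12.9 | 56% | not simulated | about 6 points (phi × 10) |
| 0.7 | 0.51 | 11.5 | 96% | 42.2% / 67.9% | about 7 points |

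The simulation used 20,000 trials per setting, 67 per arm and p = 0.35, with adjustment for baseline status by a linear-probability ANCOVA.

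**Validity of the unadjusted comparison.** In the same simulation the mean error under the null was at most 0.0014, coverage was 94.3% to 94.7%, and type I error was 5.4% to 5.7%. The adjusted analysis was also centred on the true value.

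**How unusual a 10-point imbalance is.** At p = 0.35 the baseline difference has an SE of about 8.2 points, so 10 points is 10 / 8.2 = 1.2 SE. An imbalance at least that large, in either direction, arises in a little over one trial in five.

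**Baseline status or the continuous baseline value.** A second simulation took time in range with assumed mean 65, SD 13, threshold 70, true shift 3 points and 67 per arm. At a correlation of 0.8 in the continuous measure, the SD of the risk difference was 0.084 unadjusted, 0.069 adjusted for baseline status and 0.065 adjusted for the continuous baseline. The variance cuts are 1 − (0.069/0.084)² = 33% and 1 − (0.065/0.084)² = 40%. Over correlations of 0.6 to 0.85, phi was 0.40 to 0.63. The continuous baseline is the better covariate where one exists.

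**The case against.** **The text does not say unadjusted.** A reader might infer that the plan commits to raw week-12 differences that ignore baseline. It does not. Section 2.15 names effect measures, and a risk difference can equally come from a baseline-adjusted model. This is a condensed article, and an estimator for secondary outcomes may sit in an analysis plan that is not shown. That stands for the risk-difference sentence. It does not stand for the χ² test, which is explicit, nor does it change the stated restriction of the baseline-using model to continuous outcomes.

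**Chance imbalance is not bias.** A reader might infer that chance baseline differences would be reported as treatment effect. Randomization keeps the unadjusted risk difference unbiased, and its interval already allows for chance imbalance, as the coverage figures show. What remains is a shift conditional on the imbalance that happens to occur. The issue is efficiency, not validity.

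**The outcomes are minor.** The glycemic targets are not named as between-group endpoints, and the glycemic measures behind them are also analysed as continuous key secondary outcomes. S-PPLI categories are optional. KIDMED and SCOFF are exploratory under section 2.10. Responder thresholds may be defined on change and so already use baseline. All of this stands and limits the weight of the point.

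**Not every outcome has a baseline value.** Adverse events and post-session hypoglycemia reports do not, so a blanket requirement to adjust would leave them without a method. This stands and is met in the fix.

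**Conclusion.** The point holds as a loss of precision in secondary and exploratory analyses. On the natural reading of section 2.15, categorical comparisons use no baseline information that the trial nevertheless collects. Under an assumed phi of 0.3 to 0.6, adjustment would cut the variance of the risk difference by 9% to 36%, equivalent to 10% to 56% more participants. At phi near 0 there is no gain. Neither phi nor prevalence can be drawn from the documents, so the size is conditional on those assumptions. The primary analysis and the sample size are untouched, and the unadjusted comparisons would be valid if kept.

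**What to change.** Amend the categorical-outcome sentence in section 2.15, or settle it in the analysis plan before outcome data are seen, along these lines:

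- **Binary outcomes with a baseline measurement, including responder status defined by an attained level:** marginal risk differences and relative risks by standardisation from a logistic model with randomized group and the baseline value of the same measure (continuous where it exists), with delta-method or bootstrap 95% confidence intervals. The number needed to treat is derived from this risk difference.
- **Three-level categories (KIDMED, S-PPLI):** dichotomise at a stated cut, or fit an ordinal model with the baseline value.
- **Outcomes with no baseline value, such as adverse events:** keep crude risk differences and relative risks.
- **All categorical outcomes:** show crude proportions by group as description.

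If the unadjusted comparison is preferred, say so explicitly. The cost is a few lines of text and code; no new data are needed.

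### The primary handgrip model is in effect a change-score comparison: valid, but less precise than a common-baseline model, which the plan leaves optional and ties to observed imbalance

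*Protocol article*

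**What the plan says.** Section 2.15 (Effect of the intervention) stacks the baseline and 12-week values as repeated outcomes. "Models will include fixed effects for group, time, and the group × time interaction", with random intercepts for hospital and for participant within hospital. The group × time term is the treatment effect, and the handgrip model has no further covariates. On baseline the protocol says: "Because baseline outcome values are included as repeated measurements, they will not be entered as separate covariates".

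Later in the same section: "Sensitivity analyses may include restricted longitudinal data analysis under a common-baseline assumption of baseline variables showing clinically relevant imbalance between groups". No threshold for a relevant imbalance is given.

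Sections 2.5 and 2.11 and the note to Table 2 place the baseline handgrip measurement before randomization. Questionnaires, blood and urine tests, and the 7-day insulin and carbohydrate records follow randomization. Section 2.10.1 takes the main CGM data from the 14 days before each visit.

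**The concern.** A model that keeps a free group effect at baseline subtracts the baseline value but does not otherwise adjust for it. When the baseline precedes randomization, any difference between arms at that point is chance. The model can then use one common baseline mean, or equivalently condition on the baseline value. Leaving this out has two costs. The treatment effect is estimated with more variance than the same data allow, and the estimate moves with whatever chance imbalance occurs.

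The plan names the better model but makes it discretionary and dependent on an imbalance being seen. That reverses the reasoning: randomization after the measurement justifies the constraint, whether or not the observed baselines differ.

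**Working it through.** **Inputs.** Section 2.15: "A two-sided α level of 0.05 will be used to determine statistical significance for the primary outcome". Section 2.4: "the between-group difference in handgrip strength z-score was 0.24 units, corresponding to an approximate standardized effect size of Cohen’s d = 0.56"; "Using G*Power for an independent-samples comparison with a two-sided α = 0.05"; "134 evaluable participants (67 per group) would provide 89.6% power, rounded to approximately 90"; "After allowing for an anticipated attrition rate of 15%, the recruitment target was set at 158 children and adolescents in total". Rho is not in the protocol, and Section 2.4 does not say whether d uses the SD of change or of the 12-week value.

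**Step 1, the plan's own figures.** A noncentral-t calculation with 67 per group, d = 0.56 and two-sided 0.05 gives 89.57%, matching 89.6%. Recruitment: 134/0.85 = 157.6, rounded up to 158. Both reproduce. Implied SD: 0.24/0.56 = 0.429.

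**Step 2, what the planned model estimates.** With complete data at two time points the participant and hospital intercepts cancel, and the group × time term equals the raw difference in mean change. A simulation (158 randomized, 11 hospitals, assumed ICC 0.02, 400 runs per setting) gave a maximum discrepancy of 0.0. With 15% missing at week 12 the two estimates are close but not identical (correlation 0.98 to 0.996), because participants with only a baseline value add a little information.

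**Step 3, relative precision.** With common SD σ, the variance is proportional to 2σ²(1−rho) for the planned contrast and to σ²(1−rho²) for the common-baseline model or ANCOVA. The ratio is (1+rho)/2.

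| rho | formula | simulated, complete | simulated, 15% missing |
|---|---|---|---|
| 0.5 | 0.75 | 0.748 | 0.778 |
| 0.7 | 0.85 | 0.849 | 0.869 |
| 0.9 | 0.95 | 0.950 | 0.957 |

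**Step 4, power if 0.429 is the SD of change (assumption).** Then rho = 1 − 0.429²/(2σ²), and the effective d is 0.56/√ratio, at 67 per group.

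| assumed z-score SD | rho | variance ratio | effective d | power |
|---|---|---|---|---|
| 0.8 | 0.857 | 0.928 | 0.581 | 91.6% |
| 1.0 | 0.908 | 0.954 | 0.573 | 90.9% |
| 1.1 | 0.924 | 0.962 | 0.571 | 90.7% |

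Variance therefore falls by about 4–7%. At lower rho the gain grows: power is 93.7% at rho 0.7 and 96.0% at rho 0.5.

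**Step 5, power if 0.429 is instead the SD of the 12-week value.** Planned model against common baseline: 77.6% against 92.1% at rho 0.3; 89.6% against 96.0% at 0.5; 98.6% against 99.5% at 0.7.

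**Step 6, chance imbalance.** Given a baseline difference between arms, the planned estimate shifts by −(1−rho) per unit. Simulated slopes were about −0.5, −0.3 and −0.1 at rho 0.5, 0.7 and 0.9, and within ±0.04 for the common-baseline model. With z-score SD 1 and rho 0.908, the standard error of the baseline difference is √(2/67) = 0.173. A 1-SE imbalance shifts the estimate by 0.092 × 0.173 = 0.016. A 2-SE imbalance shifts it by 0.092 × 0.346 = 0.032, or 13% of 0.24. Averaged over randomizations the shift is zero: simulated means were 0.238 to 0.245 for a true 0.24.

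**The case against.** The strongest reply is that nothing in the primary analysis is wrong. Section 2.9 defines the outcome as change in z-score, the planned contrast estimates exactly that, the model is fully prespecified, and the sample size rests on an unadjusted comparison. The planned power therefore does not depend on baseline adjustment, and on the likeliest reading the gain is one to two points on a target already met. This stands as a limit on size. It does not remove the point, because baseline adjustment uses the same data and targets the same effect.

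A reader might infer that the plan contradicts itself, since Section 2.15 also warns against choosing analyses on observed baseline differences. That sentence covers unplanned adjusted analyses chosen solely on such differences, whereas the common-baseline model is named in advance. The trigger fits poorly with the spirit of that rule but does not breach it.

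A reader might also infer that a favorable result could be substituted afterwards. The primary model is fixed, and nothing allows a sensitivity analysis to replace it.

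Finally, a reader might expect large gains across the secondary outcomes. Any figure would rest on an assumed rho. For questionnaires, blood and urine tests, and 7-day insulin and carbohydrate data, the baseline follows open-label randomization, so a common mean is not guaranteed by design. Section 3 also says that the trial is not powered for multiple secondary endpoints.

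**Conclusion.** The point holds as a matter of efficiency and prespecification. The planned handgrip analysis is essentially a change-score comparison, exactly so with complete data and nearly so with 15% attrition. It is unbiased over randomizations, and type I error is not in question.

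If 0.43 is the SD of change and the z-score SD is 0.8–1.1, the loss is about 4–7% of variance, or one to two power points. It is larger if rho is lower. Neither assumption is stated in the protocol, so this should not be read as a power failure. The misplaced trigger is a fault at any value of rho, because the timing of the measurement supports the constraint without reference to the observed baselines.

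**What to change.** - Prespecify as primary for handgrip either a constrained longitudinal model (time and group × time, no group main effect, unstructured 2×2 within-participant covariance, hospital random effect) or ANCOVA of the 12-week z-score on the baseline z-score with hospital as a random effect.
- Keep the free-baseline model as a sensitivity analysis that is always run, and delete the imbalance condition.
- Apply the common-baseline constraint also to the 14-day pre-visit CGM outcomes. Do not apply it to questionnaires, blood and urine tests, or 7-day insulin and carbohydrate data.
- State in Section 2.4 whether d = 0.56 uses the SD of change.

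The cost is wording in the protocol and analysis plan. Data, visits, sample size and the effect being estimated stay the same, provided the change is made before the data are analyzed.
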